## Abstract

**Background:**

Emotional dysregulation and impaired attachment are potential contributors to the development of psychopathology in adolescence. This raises the question of whether oxytocin (OT), the paradigmatic “attachment hormone,” may be beneficial in such contexts. Recent evidence suggests that intranasal administration of OT increases affiliative behavior, including trust and empathy. OT may also facilitate social reciprocity by attenuating the stress response to interpersonal conflict. To date, few studies have investigated the effects of intranasal oxytocin (IN-OT) on neurophysiological emotion regulation strategies in healthy adolescents, particularly during parent-adolescent interaction. To understand these mechanisms, our study will examine the effects of IN-OT on emotion regulation in adolescents during parent-adolescent stressful interactions, and on each adolescent’s visual and neurophysiological strategies when visualizing attachment-related pictures. We hypothesize that IN-OT will influence psychophysiological outcomes under conditions of stress. We predict that IN-OT will momentarily increase feelings of safety and attenuate stress and hostile behavior during conflict situations. OT may also enhance attachment security by increasing comfort and proximity-seeking, and reducing neurophysiological hyperactivation.

**Objective:**

The objective of this study is to evaluate the effects of IN-OT on insecure adolescents by studying their behavior and discourse during a disagreement with one of their parents. Their neurophysiological responses to pictures eliciting attachment-related emotions and their visual exploration strategies will also be investigated.

**Methods:**

In this randomized, double-blind, placebo-controlled parallel-group design, 60 healthy male adolescents classified as insecurely attached will receive 24 international units (IU) of IN-OT versus placebo (PB), 45 minutes before the experimental tasks. Each adolescent will then be invited to engage in an experimental conflict discussion with one of his parents. The conflict session will be videotaped and coded for verbal and non-verbal interaction behavior, using the Goal-Corrected Partnership in Adolescence Coding System (GPACS). Each adolescent will then be asked to visualize attachment-related pictures on a screen. Eye-tracking (ET) and neurophysiological responses, including electrodermal activity (EDA) and heart rate (HR), will be recorded simultaneously and continuously during attachment-related picture viewing (Besançon Affective Picture Set-Adolescents, BAPS-Ado).

**Results:**

Enrollment for the study was completed in May 2016. Data analysis commenced in July 2016. Study results will be submitted for publication in the winter of 2017.

**Conclusions:**

OT is a complex molecule with many facets that are not yet fully understood. This experimental protocol will increase scientific and clinical knowledge of emotion regulation skills in insecure adolescents by assessing the impact of IN-OT on parent-adolescent interaction and on the visual processing of attachment-related emotions. Positive results could lead to therapeutic uses of IN-OT to treat emotion dysregulation in adolescence.

## Introduction

### Background

Adolescence is a period of psychobiological and social changes necessary to achieve psychological maturation and develop autonomy [1,2]. However, because of their history and temperament, some adolescents will have difficulty regulating their emotional reactivity, which could lead to emotional dysregulation and mental suffering when emotions are too intense or violent. This emotional dysregulation can be associated with psychopathology, such as depression [3], eating disorders [4], substance abuse [5], or antisocial and delinquent behavior [6]. In recent years, the impact of attachment bonds on adolescent emotional (dys)regulation has been seriously questioned.

Attachment has been defined as an innate psychobiological system that motivates people to seek proximity in times of distress [7-9]. The quality of this system is determined by early caregiving experiences and results in individual differences in attachment security. Harmonious attachment experiences can result in secure attachment, while disordered experiences can lead to insecure (ie, avoidant or anxious) or disorganized attachment [10]. Attachment patterns become part of the general interpersonal style that will influence strategies of closeness-distance regulation toward the attachment figure, as well as strategies of emotion regulation [11,12].

Despite the change in parent-child interaction during the process of adolescence, where more distance and more conflict linked with autonomy occur, parents remain a secure base for the adolescent in times of distress. It is expected that parents will continue to offer a protective base to help adolescents to regulate their emotions and to sustain a “goal-directed partnership” with them. This relationship context, in which adolescents might experience disagreement situations and develop a variety of emotional responses to deal with potentially elicited distress, is linked to the attachment style of the adolescent [13-16].

Social attachment interaction has health benefits, and its absence can be associated with both physical and mental illness, with broad consequences throughout the lifespan [17]. Researchers have shown that a securely attached adolescent reports less conflict with parents and fewer psychopathological symptoms [18-20]. During conflictual exchange, secure adolescents display collaborative communication, while also expressing anger and hostility. In this context, secure adolescents feel safe to communicate differences of opinions and vulnerabilities with trust and openness [14]. In contrast, insecurely attached, avoidant adolescents display deflecting and/or minimizing attachment strategies during interaction with their parents. They tend to manifest distracted and disengaged behavior and to elaborate on their disagreement, maintaining emotional distance, instead of reciprocity. Adolescents with ambivalent attachment may present entangled and/or oscillatory interactions. Here, the adolescent may manifest distressed or frustrated behavior when facing awkward reciprocity and parental inconstancy [21,22]. These two insecure attachment patterns could become risk factors for emotional dysregulation linked to a broad spectrum of psychopathology (eg, anxiety, depression, conduct disorders). Finally, disorganized parent-adolescent dyadic interaction is characterized by the inability to collaborate, marked by an unbalanced relationship, characterized by different profiles, such as role-confusion or hostile/passive patterns [23].

Recent findings suggest that a common neurobiological system appears to underlie attachment via release of various neuropeptides, the main one being oxytocin (OT) [24]. OT, synthesized in the magnocellular neurons of the supraoptic and paraventricular nuclei of the hypothalamus, projects to the posterior pituitary [25], where it is released into the bloodstream causing a wide range of bodily effects [26-28]. Within the brain, OT can act as a neurotransmitter and/or neuromodulator in various limbic, midbrain, and hindbrain structures [29]. Its central neuromodulatory role in sexual behavior [30], lactation, and childbirth [31] is increasingly recognized. Due to its role in parent-child bonding [32], empathy [24,33,34], trust [35,36], and the promotion of social behavior [37], OT has earned a strong popular and scientific reputation as the “hormone of love” or “hormone of attachment” [38].

These discoveries have led researchers to investigate the effects of intranasal oxytocin (IN-OT) within the healthy [39-45] and clinical [46-49] population. However, it appears that IN-OT can be more beneficial for some individuals than for others, and that the effects of IN-OT seem to be moderated by contextual factors (eg, presence of stranger versus friend [50]), and individual factors (eg, differences in attachment [39,43,44,51-57]). Individual attachment differences have proved to be a strong modulator of OT action [49,55,56], and mediate stress-buffering effects in times of stress [58]. Interestingly, the effects of OT appear to be moderated by attachment anxiety level [40]. In highly preoccupied anxious individuals, OT appears to exacerbate interpersonal insecurity and to affect how the quality of maternal interaction is remembered. After IN-OT administration, highly preoccupied individuals remembered their mothers as less caring and less close, while less anxiously attached individuals remembered their mothers as more caring and more close [40]. The level of attachment avoidance also seems to influence IN-OT effects. In highly avoidant individuals, IN-OT has been shown to increase constructive interaction [52]. For example, under the placebo (PB) condition, avoidant males trusted an unknown protagonist less, feared betrayal more, and decided less often to approach their protagonist cooperatively. However, these effects of attachment avoidance disappeared when males received IN-OT prior to decision-making. Participants high in attachment avoidance show more trust, lower betrayal aversion, and they cooperated more when given IN-OT rather than PB. Other findings [44] have shown that individual differences in attachment act as an endophenotype that moderates the effects of the OT system on social behaviors and cognition following social exclusion. OT appears to contribute to ongoing cooperation with a rejecting but initially cooperative partner, but only for those with low attachment avoidance [44]. Recent research [39] has shown that IN-OT increases communion skills in avoidantly attached individuals, who were especially likely to perceive themselves as more kind, warm, and gentle after receiving IN-OT than after receiving the PB. There was also a major effect of IN-OT on agency [59] in anxiously attached individuals, who showed a selective decrease in independent, self-confident behavior following IN-OT administration. This variability in IN-OT effects raises many questions and controversies regarding the effects of this hormone on social interaction, and especially on the influence of moderating factors. This lack of consensus together with many inconsistent results have led researchers [60-62] to openly question the true impact either of IN-OT in general or of its potential therapeutic effect [63]. Thus, to better understand the effects of OT and the impact of moderating factors on the mechanisms of socio-emotional interaction, we propose an original study protocol that provides new avenues of research into OT from both social and emotional perspectives.

### Current Study

This study protocol seeks to examine the effects of IN-OT administration on emotion regulation strategies in insecure adolescents. A reliable protocol is crucially needed in the field of attachment and OT research, if we want to build a solid theoretical background for interpreting OT, before IN-OT can be proposed as adjuvant therapy in insecure adolescents with emotion dysregulation. We hypothesize that IN-OT will promote a “momentary” subjective experience of attachment safety and proximity-seeking in insecurely attached adolescents during dyadic stressful interaction. We suppose that both anxious and avoidant adolescents under treatment will communicate with their parents with more self-disclosure, and will manifest less negative (eg, controlled, hostile, odd) behavior than under the PB condition. We suppose that IN-OT will positively bias parent-adolescent interaction, especially for highly anxious individuals, because it should attenuate their chronic concerns about distress, separation, and abandonment. OT might support parent-adolescent interaction and emotion regulation for highly avoidantly insecure adolescents (often suspicious and defensive), who avoid expressing emotions in the family context. We hypothesize that, in general, insecurely attached adolescents under IN-OT will process attachment-related emotional information in a more accessible and open way compared to PB conditions. Compared to the PB, IN-OT will increase exploration of distress and comfort pictures (eg, first fixation duration; number and duration of fixations). During visualization of distress pictures, IN-OT will attenuate emotional arousal by decreasing neurophysiological reactivity (amplitude of specific skin conductance response, SCR), and should also decrease SCR and decelerate heart rate (HR).

The main objective is to evaluate the effect of IN-OT on the behavior and discourse of insecure adolescents during a disagreement (stressful situation) with one of their parents. This evaluation will be based on the average score on the scales (4 negative and 1 positive) of the Goal-Corrected Partnership in Adolescence Coding System (GPACS) (personal communication from [name], author of the GPACS). Secondary objectives will be to evaluate the effect of IN-OT versus PB on visual exploration strategies for images eliciting attachment-related emotions (ie, distress and comfort). This characterization will be based on the study of eye parameters (ie, total picture fixation time, and average number of fixations per emotion) assessed by a remote eye tracking (ET) device.

We are conducting a randomized, double-blind, placebo-controlled protocol in which insecure adolescent male participants received IN-OT or PB. The protocol was designed to investigate the effects of IN-OT on emotion regulation strategies, by testing whether attachment anxiety and avoidance moderate the effects of IN-OT during a conflict discussion with a parent, and during the visualization of attachment-related pictures.

Emotion (dys)regulation strategies will be evaluated through a multi-dimensional approach: ET and neurophysiological measurements including electrodermal activity (EDA) and HR. These neurophysiological measurements have recently received a great deal of attention as potential biological markers of individual differences in affective response [64,65]. HR reflects the continuous interplay between the sympathetic and the parasympathetic nervous systems and is regarded as a measure of autonomic flexibility and even as a biological marker of emotional response [65]. SCR, a form of EDA, is supposed to primarily reflect autonomic arousal, regardless of the state induced by the stimulus, whether negative or positive [64]. Changes in SCR represent activity within the sympathetic axis of the autonomic nervous system (ANS), measured by autonomic innervations of the skin sweat glands [66]. The neurobiological underpinnings of SCR are widespread and not exclusively related to the defense network. Likewise, HR is also under the control of the ANS [67]. Deceleration of HR is often shown in response to affective stimuli, and is more pronounced in reaction to negative stimuli [67]. HR deceleration seems to be more closely related to attentional processing regarding changes in affective states rather than to valence or arousal [68]. In summary, SCR and HR represent different neural systems, thus allowing us to assess more accurately the effects of OT in response to attachment-related emotions.

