### Parent-Adolescent Interaction Assessment

The quality of the parent-adolescent interaction will be assessed with the French version of the GPACS. The development of the GPACS drew on prior literature describing behavioral manifestations of security, insecurity, controlling behavior, and behavioral disorganization among younger children toward their parents in stressful situations. It has already been used in several studies [77-79]. The GPACS coding system includes the rating of each interaction on 10 5-point scales from 1 (not at all) to 5 (very much). There are 2 positive scales (1) “Collaborative Communication” indexing cooperative goal-corrected partnership and parent/adolescent carefulness; and (2) “Caregiving Validation of Adolescent’s Voice” indexing the caregiver’s support for the adolescent. There are 8 negative scales characterizing 3 subtypes of disorganized interaction (ie, punitive, caregiving/role confusion, and disoriented behavior). These 8 scales are (1) parental punitive behavior (eg, angry, critical or mocking comments about the adolescent); (2) adolescent punitive behavior (eg, angry, critical or mocking comments about the parent); (3) adolescent disoriented-distractible behavior (eg, suddenly stopping in midsentence and “freezing” with hand in midair or pausing abruptly in mi-sentence); (4) parental disoriented behavior (eg, the same as adolescent disoriented behavior); (5) adolescent odd, out-of-context or contradictory behaviors, which may seem disjointed, startling, or inexplicable to an observer (eg, using a forced, high-pitched, or childish tone of voice, shifting into unusual, fantasy-based topics); (6) parent odd, out-of-context behavior (eg, using a forced, high-pitched, or childish tone of voice, wandering around the room, stiff, usually shifting away from the topic); (7) adolescent attempts to manage or take care of the parent or modulate the parent’s behavior (eg, offering guidance, defusing tension with over-bright, entertaining behavior); and (8) parental role confusion (eg, asking for advice on topics typically discussed with partner or other adult).

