### Outcomes

#### Primary Outcome

The primary outcome is the evaluation of the changes in adolescent-parent interaction using GPACS in the OT versus PB conditions.

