### Data Analysis

#### Statistical Power, Establishment of Sample Size, and Safety

The calculation of sample size will be based on the average score on the 4 negative dimensions (items) of the GPACS between the group of adolescents who will receive treatment with OT and the group that will receive the PB. No clinical studies have used this scale in an attachment study, so this calculation is based on expert opinion (personal communication from [name], author of the GPACS). We estimate that a difference of 5 points for our main criterion is an interesting minimum clinical difference. Based on the supposition of a difference of 5 points for the OT group, a standard deviation value of 6.2 was calculated. We do not have the standard deviation of the values on our primary endpoint. However, we have the standard deviation of each negative item in the GPACS and summarized data from the original validation study of the GPACS. The variability of the values obtained for each of the 4 negative items were summed and we obtained a variability of 0.03 (SD 0.175). If we consider that the sum represents 3% of the total variability (co-variations to be added), then we arrive at a standard deviation of 6.2, a 90% power and an alpha level of 5% unilateral (superiority of trial against PB); therefore 54 patients should be included. Taking into account 10% of error and non-analyzable data, 60 patients should be included (ie, 30 patients per group). The overall significance level of statistical tests will be at 5%.

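### The primary GPACS score is defined with five scales in one section and four in another, and an unreversed positive scale would dilute the hypothesised effect

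*Protocol article*

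**What the plan says.** Four places in the Protocol article bear on the primary score.

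- **Current Study**: the main objective will be evaluated "based on the average score on the scales (4 negative and 1 positive) of the Goal-Corrected Partnership in Adolescence Coding System (GPACS". That is five scales, pointing in two directions. The positive scale is not named.
- **Statistical Power, Establishment of Sample Size, and Safety**: the calculation is "based on the average score on the 4 negative dimensions (items) of the GPACS". That is four scales in one direction. The section treats this score as the main criterion and gives it a minimum difference of 5 points and an SD of 6.2.
- **Primary Outcome**: "The primary outcome is the evaluation of the changes in adolescent-parent interaction using GPACS in the OT versus PB conditions". No scales are named.
- **Parent-Adolescent Interaction Assessment**: the instrument involves the "rating of each interaction on 10 5-point scales from 1 (not at all) to 5 (very much", so a higher rating always means more of the behaviour. Two scales are positive. On the others, "There are 8 negative scales characterizing 3 subtypes of disorganized interaction"; by description, four of these rate the adolescent and four the parent.

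On direction, Current Study predicts more self-disclosure under oxytocin and that the adolescents "will manifest less negative (eg, controlled, hostile, odd) behavior than under the PB condition". The Procedure section describes one interaction session, held after dosing, with no GPACS rating before it.

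**The concern.** A trial has one primary score, and this article gives two that are not interchangeable. The difference and SD behind the sample size belong to the four-scale score; none are given for the five-scale one. If the analysis follows Current Study, the trial tests an endpoint it was not sized for.

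The two definitions also respond differently to the predicted benefit. In a plain average of four negative scales and one positive, a fall in hostile behaviour lowers the score and a rise in open communication raises it, so part of the benefit offsets the rest. The article mentions neither reversal nor separate analysis of the positive scale.

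While both definitions stand, whether the positive scale counts, and in which direction, could be settled after results are seen.

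**Working it through.** **1. The plan's own figure.** Inputs from the sample-size section: difference 5, SD 6.2, one-sided 5%, power 90%. Per arm, n = 2 × (6.2/5)² × (1.645 + 1.282)² = 2 × 1.5376 × 8.56 ≈ 26.3, rounded up to 27. Both arms give 54, and 54/0.90 = 60. A noncentral t check at 27 per arm gives 90.0% power. The stated numbers reproduce, and they belong to the four-scale score.

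**2. Raw effect under each definition.** Let each negative scale fall by x and the positive scale rise by g·x.

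- Four negative scales: mean change −x.
- Five scales, positive unreversed: (−4x + gx)/5.
- Five scales, positive scored as 6 minus the rating: (−4x − gx)/5.

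For the unreversed average the change is −0.7x at g = 0.5, −0.6x at g = 1 and −0.4x at g = 2. It is zero only at g = 4, when the positive scale rises by as much as the four negative scales fall in total. With the positive scale reversed and g = 1, the change is −x, so nothing is lost.

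**3. Standardised effect.** The documents give no correlations. Assume equal item SDs, correlation r among negative scales and −r between each negative scale and the positive one. In units of the item variance:

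- four-scale mean: (4 + 12r)/16
- unreversed five-scale mean: (5 + 12r − 8r)/25 = (5 + 4r)/25

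The ratio of standardised effects at g = 1 is 0.6 × SD₄/SD₅:

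| r | SD₄ | SD₅ | Ratio |
|---|---|---|---|
| 0 | 0.500 | 0.447 | 0.67 |
| 0.3 | 0.689 | 0.498 | 0.83 |
| 0.5 | 0.791 | 0.529 | 0.90 |

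The result is sensitive to g. Replacing 0.6 by 0.7 (g = 0.5) gives 0.78, 0.97 and 1.05. A small rise on the positive scale with strongly correlated items therefore costs nothing in standardised terms.

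**4. Metric.** A mean of 1-to-5 items lies between 1 and 5, so two group means differ by at most 4 and the SD cannot exceed (5 − 1)/2 = 2. A 5-point difference and an SD of 6.2 are both impossible for it. A sum of four items runs from 4 to 20, with a largest difference of 16 and a largest SD of 8. The planning figures could fit only a sum, although both sections call the score an average.

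**The case against.** The article condenses a fuller protocol. The five-scale wording is one sentence in its introduction, and an average score on the scales could mean scale-by-scale means. Reversal is not stated, but neither is it excluded, and scoring direction is a detail often left to the analysis plan. All of this stands: the silence on reversal is not an error in itself, and the dilution is conditional. It does not remove the conflict, because two different scale sets are printed and an unseen document can agree with at most one.

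A reader might infer that averaging opposite-direction scales cancels the benefit. Step 2 does not support that: equal movement loses 40% of the raw effect, and full cancellation needs g = 4.

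A reader might also carry 5/6.2 = 0.81 through step 3 and conclude that power drops from 90% to between 62% and 84%. The documents do not support that either. The 5 and 6.2 cannot describe the average to which they are attached. If they describe a four-item sum with equal item SDs of at most 2, then 6.2² = 38.44 ≤ 4 × (4 + 12r) requires r of at least 0.47, so the low correlations that produce the worst power figures would not apply.

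On which four scales are meant, the objective concerns the adolescent's behaviour and exactly four negative scales rate the adolescent, so these are the natural candidates. The article does not say so. The reference to changes in the Primary Outcome section reads naturally as a between-arm difference in a parallel-group trial, and is not a separate fault.

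**Conclusion.** The inconsistency is established from the text alone: five scales in the main objective, four in the sample-size section, none named in the primary outcome. It concerns the primary endpoint and must be resolved.

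The dilution holds only if the positive scale enters a single average unreversed, which the wording suggests but does not confirm. On that reading, with equal movement on all scales, the raw effect shrinks to 0.6 of its size and the standardised effect to about 0.67 to 0.90 of the four-scale value. The second range rests on assumed equal SDs and correlations of 0 to 0.5 and is illustrative; it supports no statement about the trial's actual power. The sample-size arithmetic is correct for its inputs, but those inputs are not on the metric the article names.

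**What to change.** Before unblinding, state one primary endpoint in identical words in Current Study, Primary Outcome and the sample-size section:

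- the score on the four adolescent negative scales (punitive; disoriented-distractible; odd or out-of-context; managing or taking care of the parent), once the sponsor confirms that these are the four intended;
- compared between arms at the single post-dose session;
- with the positive scale named and kept as a separate secondary endpoint, not averaged in.

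State whether the score is a sum (4 to 20) or a mean (1 to 5), and give the difference and SD on that metric. If 5 and 6.2 were meant for the four-item sum, they can stay with a sum, or become 5/4 = 1.25 and 6.2/4 = 1.55 for a mean. Their ratio, and so the 54 and 60, would not change. If they were not meant for that sum, the sample size needs a fresh justification.

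The cost is wording and a check on where the planning figures came from; no new data are needed. The Abstract says analysis commenced in July 2016 while the Results section says it will commence, so the sponsor should state whether unblinding has occurred. If it has, the report should say which definition was fixed beforehand and show the result under both.
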